### Research compliance and regulatory audit

The regular research compliance and regulatory audit of this study will be conducted at GHS and performed by Corporate Compliance. The scope of the audit will include a review of internal controls through inquiry and detailed sample-based testing of the following processes: registration, visit charge, research study charge capture and billing. The investigators’ research records and the corresponding approved Institutional Review Board (IRB) documents will be reviewed to strengthen awareness of regulatory requirements and improve the ethical conduct of research. A copy of research regulatory findings will be sent to the GHS IRB.

### Data management and data sharing

The Study data will be collected through RedCap (study specific survey data) and EPIC (clinical data), which will be maintained at GHS. Regular data review/reports will be generated through the RedCap and EPIC to monitor the patient enrollment, group balance, compliance, and the time to make the reminding calls & patient incentives. The study related raw data will be transferred to Clemson University (every 6 months) for further data merging and cleaning. The merged datasets will be stored and maintained at Clemson University during the study active period. A virtual machine (VM) will be allocated for hosting the data raw and computation. Clemson University Clemson Computing and Information Technology (CCIT) will be responsible for the security management of the VM. The Clemson University research team will be responsible for data merge and cleaning. The cleaned dataset will be shared with GHS team.

The Study recognizes the final National Institutes of Health’s Statement on Sharing Research Data (NIH Guide: February 26, 2003; Notice # NOT-OD-03032). This Statement recognizes that the rights and privacy of people who participate in NIH-sponsored research must be protected at all times including in the course of sharing data. The Statement further recognizes that the PIs are granted sufficient time in which to analyze and publish their primary research initiatives. To support NIH’s long-standing policy to share and make available to the public the results and accomplishments of the activities that it funds, the study team has developed the following data sharing plan and has been approved by NIH. Data will be shared with NIH according to NIH existing policy. Before any data is sent to NIH, all personal identifiers will be removed and a unique study number will be assigned that is different from the study ID number used by our team to add a second level of security to protect participant confidentiality. Data sets from different sources (i.e. laboratory, screening, questionnaire) will be created using SAS, with each participant’s data linked using the unique study ID. Each data set will be labeled. A data dictionary of variable labels and codes will also be provided. We propose the use of SAS data files with accompanying data dictionaries; however other data systems can be used to prepare these files if preferred (such as, EXCEL, SAS or STATA). In addition, before a public use data set is created, data staff will review all fields to ensure that there are no fields that might reveal the identity of a subject. For example, providing zip code, race, and date of birth on a subject may be used to reveal the identity of a subject if the combination is unique.

### Sample size

We calculated our sample size based on Aims 1 & 2 with the primary outcome of PTB. Based on the literature and our preliminary data, the rate of PTB was approximately 10-16% of women in the traditional care setting [16]. The odds ratio of comparing PTB in GPNC to IPNC was 0.67 in the Ickovics study and 0.53 in our own study [16, 17]. Our own work also suggests that the risk difference of having PTB between Black women and White women was 1.0% in the IPNC and 2.4% in the GPNC. Taken together, it is reasonable to assume that the relative risk of PTB in the IPNC group could range from 10% to 16%. For aim 1, assuming the proportion of PTB rate of 13%, our study will need *N* = 2,712 (1,356 in each group) to detect the relative risk of PTB in GPBC vs. IPNC of 0.70 with an alpha of 0.05 and a power of 90%. For aim 2, assuming the proportion of PTB rate of 0.02, our study will need *N* = 2,748 (1,374 in each group) to detect reduction in risk difference of 1.4% between Black and White women in GPNC vs. IPNC group with an alpha of 0.05 and a power of 90%. With an estimated 15% attrition rate, we will target recruiting 3,160 (*N* = 1,580 in each group) women for this study. Table 3 gives the estimated minimum number (in each group) required to achieve an alpha of 0.05 and a power of 80% or 90% to detect the risk ratio from 0.5 to 0.7 in Aim 1 and to detect the risk difference from 0.01 to 0.08, given the rate difference (P_0_) of preterm birth between Black women and White women at the IPNC group ranges from 2% to 3% in Aim 2, This sample size estimates that the proposed study will have 90% power to detect racial difference on PTB for Aim 2.

**Table 3 Tab3:** Sample size and power calculations

	Power = 80%			Power = 90%		
Aim 1	RR = 0.50	RR = 0.60	RR = 0.70	RR = 0.50	RR = 0.60	RR = 0.70
P_0_ = 0.10	435	721	1,356	582	965	1,814
P_0_ = 0.13	326	540	1,014	436	723	1,356
P_0_ = 0.16	258	427	800	345	571	1,070
Aim 2	RD = 0.01	RD = 0.014	RD = 0.018	RD = 0.01	RD = 0.014	RD = 0.018
P_0_ = 0.02	2,319	1,027	526	3,103	1,374	704
P_0_ = 0.03	3,826	1,799	995	5,121	2,048	1,332
P_0:_ the RD of PTB in IPNC group; RR: relative risk						

Abbreviation: RD = risk difference

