### Preliminary research

In 2012, we published a retrospective study of 316 women who participated in GPNC compared with 3,767 women in IPNC [16]. The adjusted odds ratio for PTB for women in GPNC care was 0.53 (95% CI: 0.34, 0.81) as compared to women in the IPNC. The racial disparity in PTB between Black women and White women was also diminished for women in GPNC: the Black-White difference of PTB was 1.0% in the GPNC and 2.4% in the IPNC group. In 2012–2013, we conducted a mixed methods prospective cohort study comparing the effectiveness of GPNC to IPNC on women’s psychosocial health [24, 33]. We recruited 248 women, retaining 89% of participants through pregnancy and 84% into the postpartum period. Women completed surveys at two points during pregnancy and once in the post-partum period. Among women with inadequate initial social support, GPNC participants scored 3.16 points lower (*P* = 0.03) on a scale of prenatal distress in late pregnancy. Among women with high initial prenatal distress, GPNC participants scored 7.96 points higher (*P* = 0.008) on a measurement of planning and preparation coping in late pregnancy [24].

Preliminary data from our retrospective and prospective studies demonstrate the potential for GPNC not only to reduce PTB, but also to reduce racial disparities in PTB. Our preliminary data also indicates that GPNC improves women’s psychosocial outcomes as well, particularly for those reporting high levels of stress in early pregnancy. By using a RCT design, this proposed study will reduce the possibility of selection bias and influences from potential confounding, and have adequate power to conclusively assess the efficacy of GPNC compared with IPNC on rates of PTB and racial disparities in birth and other outcomes among White and Black women.

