### Specific aims and hypotheses

The proposed study will employ a RCT design adequately powered to detect difference in PTB by intervention and race. The study will be conducted in a large prenatal care provider in South Carolina (SC), with historically high PTB rates of 16.4%. The proposed study builds on an established research program focused on assessing the impact of GPNC vs. IPNC on birth outcomes and will investigate the following Specific Aims:

### Specific Aim 1

To compare the rate of PTB prior to 37 weeks gestational age and other selected birth outcomes and pregnancy complications (e.g. birth weight, caesarean section rate) among women who participate in CenteringPregnancy GPNC to their counterparts in IPNC.

#### Study hypothesis 1

Women who participate in GPNC will have a lower rate of PTB and other improved birth outcomes as compared to their counterparts in IPNC.

### Specific Aim 2

To compare the risk difference of PTB and other selected birth outcomes of Black women vs. White women in GPNC to the risk differences of Black women vs. White women in IPNC.

#### Study hypothesis 2

The risk difference of PTB and other selected birth outcomes between Black and White women in the GPNC group is smaller than that in the IPNC group.

### Specific Aim 3

To compare whether women in the GPNC have improved maternal psychosocial (i.e. activation, engagement, stress) and behavioral (i.e. smoking, healthy eating, health practices) outcomes as compared to their counterparts in IPNC and to explore whether improving certain maternal psychosocial and behavioral outcomes will explain the potential benefits of GPNC on racial disparities in birth outcomes.

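### The Sample size section reverses the arms of the preliminary Black-White gaps, and its unqualified 90% power for Aim 2 does not hold at those gaps even by its own formula

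*Protocol article*

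**What the plan says.** The Preliminary research section reports from the retrospective cohort that "the Black-White difference of PTB was 1.0% in the GPNC and 2.4% in the IPNC group", and describes the disparity as diminished under group care.

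Hypothesis 2 runs the same way: the gap "between Black and White women in the GPNC group is smaller than that in the IPNC group".

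The Sample size section describes the same work as showing that "the risk difference of having PTB between Black women and White women was 1.0% in the IPNC and 2.4% in the GPNC".

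For Aim 2 it then proceeds by "assuming the proportion of PTB rate of 0.02" and arrives at "2,748 (1,374 in each group) to detect reduction in risk difference of 1.4% between Black and White women in GPNC vs. IPNC group", with alpha 0.05 and 90% power. The Table 3 footnote defines P0 as the risk difference in the IPNC group. The text describing Table 3 says that the rate difference "of preterm birth between Black women and White women at the IPNC group ranges from 2% to 3% in Aim 2".

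The paragraph closes: "This sample size estimates that the proposed study will have 90% power to detect racial difference on PTB for Aim 2".

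**The concern.** There are two separate faults.

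The first is one of fact. The Sample size section puts the preliminary gaps in the wrong arms. Read literally, the evidence offered for Aim 2 shows group care making the disparity worse.

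The second is one of inputs. The planned reduction of 1.4 points equals 2.4% minus 1.0%, the two preliminary gaps. The control value paired with it is 2.0%, not 2.4%, and no reason is given. The implied GPNC gap of 0.6% appears nowhere in the article. In the formula used, the same absolute reduction from a lower base needs fewer women, so the choice favours the stated power.

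At stake is how far the 90% figure can be relied on. The aims section presents the trial as adequately powered for differences by intervention and race, and the Aim 2 total of 2,748 (against 2,712 for Aim 1) is the larger one, from which 3,160 follows. A null result for Aim 2 would be read against that 90%.

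**Working it through.** **Inputs.** Preliminary gaps: IPNC 2.4%, GPNC 1.0% (Preliminary research). Planning values: P0 = 0.02, reduction 0.014, alpha 0.05, power 90%, 1,374 per group, 15% attrition, 1,580 per group recruited (Sample size). Allocation 1:1 (Randomization). Sidedness is not stated; two-sided reproduces the printed figure, while one-sided gives 1,120.

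**Direction.**

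| Place | IPNC gap | GPNC gap | Effect of group care |
|---|---|---|---|
| Preliminary research | 2.4% | 1.0% | narrows by 1.4 points |
| Sample size, text | 1.0% | 2.4% | widens by 1.4 points |
| Sample size, calculation | 2.0% | 0.6% (implied) | narrows by 1.4 points |

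The text on preliminary data in the Sample size section is the only place where the gap widens.

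**Formula.** The printed figures come from the usual two-proportion formula with pooled variance and no continuity correction, with the two gaps entered as if they were proportions:

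n = [1.960 × √(2p̄(1−p̄)) + 1.282 × √(p1(1−p1) + p2(1−p2))]² / (p1−p2)²

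**The plan's own figure.** p1 = 0.020, p2 = 0.006, p̄ = 0.013:
- 1.960 × √0.025662 = 0.3140 and 1.282 × √0.025564 = 0.2049
- n = (0.5189)² / (0.014)² = 1,373.6, printed as 1,374.

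The formula is symmetric in p1 and p2, so exchanging the arm labels leaves n unchanged.

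**The preliminary gaps.** p1 = 0.024, p2 = 0.010, p̄ = 0.017:
- 1.960 × √0.033422 = 0.3583 and 1.282 × √0.033324 = 0.2339
- n = (0.5923)² / (0.014)² = 1,789.7, so 1,790 per group (3,580 in total), 30% more than 1,374.

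Power for 2.4% vs 1.0% is Φ of [0.014√n − 0.3583] / √0.033324:

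| Per group | Basis | Power |
|---|---|---|
| 1,374 | stated requirement | 81.1% |
| 1,343 | 1,580 × 0.85 | 80.2% |
| 1,580 | no attrition | 86.1% |

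Even with no attrition, 90% is not reached.

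**What Table 3 already shows.** At P0 = 0.03 with a reduction of 0.014 it prints 1,799 per group for 80% power and 2,048 for 90%. (The formula gives 2,408 for the latter.) Both printed figures exceed 1,374.

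**Why 81% is not the real power.** The analytic plan tests a treatment-by-race interaction among Black and White women only. On the risk-difference scale its variance is the sum of p(1−p)/n over four arm-by-race cells, with p being preterm birth rates of the order of 10%, not gaps of 1% to 2%. As an illustration, assume an overall IPNC rate of 13%, a White IPNC rate of 11.8%, a White GPNC rate 0.7 times that (8.26%), gaps of 2.4% and 1.0%, and 1,374 per group with the 45.8% White and 25.5% Black shares in the Patient population section. The standard error is then 2.96 points, 1.4/2.96 = 0.47, and power is about 8%. Across IPNC rates of 10% to 16%, power is about 7% to 8% with those shares and 8% to 10% with a 50:50 split. These rates are assumptions; they show only that the two-proportion formula does not describe the planned test.

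**The case against.** The strongest reply is that nothing here is a calculation error. P0 = 0.02 is openly stated as an assumption, and 1,374 is exact for it. A planning value need not copy a preliminary estimate: Aim 1 does not do so either, taking a relative risk of 0.70 although the group's own study gave an odds ratio of 0.53. This stands. What remains is that the 1.4-point reduction equals the preliminary one while the base does not, the base is the favourable end of the tabulated range, and no reason is offered.

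A reader might infer that the reversed arms made the sample size wrong. They did not: the formula is symmetric, and the calculation itself runs in the intended direction.

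A reader might also infer that the plan claims 90% power across the whole 2% to 3% range. The text does not support that. The range belongs to the sentence describing Table 3, the 90% statement is a separate sentence about the chosen sample size, and Table 3 itself shows that 1,374 is too few at P0 = 0.03. The fault is that the closing sentence is not tied to 2.0% vs 0.6%.

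Finally, the effect on recruitment is small. Aim 2 exceeds Aim 1 by 36 women, and 2,712 × 1.15 is about 3,119 against 3,160. Aim 1's power is untouched. This also stands.

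**Conclusion.** The point holds in two limited parts.

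The Sample size section misreports the preliminary gaps by reversing the arms, against the Preliminary research section, hypothesis 2 and its own planned reduction. This has no numerical consequence.

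The unqualified 90% power for Aim 2 does not hold at the trial's own preliminary gaps. By the plan's formula it is about 81% at 1,374 per group, 80% after the stated attrition and 86% with none. This rests on a two-sided alpha of 0.05 and on the formula that reproduces 1,374.

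It would be a mistake to take 1,790 per group as an adequate size for Aim 2, or 81% as its power. Both only test the section against its own method, which enters risk differences as proportions and does not match the planned interaction test.

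**What to change.** 1. Correct the sentence in the Sample size section to 2.4% in IPNC and 1.0% in GPNC.
2. Withdraw the unqualified statement of 90% power for Aim 2. At most it may be said that, by the formula used, 1,374 per group gives 90% for 2.0% vs 0.6%.
3. Restate the Aim 2 power at the planned 3,160 from the 2.4% and 1.0% gaps, calculated for the treatment-by-race comparison among Black and White women, with the assumed preterm birth rate in each race and arm and the expected numbers of Black and White women. Do not restate it by putting 2.4% and 1.0% into the two-proportion formula, since 80% to 86% would be another unsupported figure.

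The cost is one reworded paragraph, one new power calculation and a less favourable stated power for Aim 2. No change in sample size is asked.

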### Patient population

The target population consists of medically low-risk pregnant women of different races/ethnicities. In our retrospective cohort study published in 2012, our study population in the comparison group included 45.8% non-Hispanic White, 25.5% non-Hispanic Black, 22.2% Hispanic and 6.5% “Other” race/ethnicity [21]. We expect that our current study population will be similar.

To be eligible for this study, women will 1) be between 14–45 years of age, and 2) enter prenatal care before their 20^th^ week of gestation. Study exclusion criteria include 1) medical complications of pregnancy which would preclude prenatal care provision by nurse practitioners or participation in group care (e.g. pre-gestational diabetes, severe chronic hypertension, active pulmonary tuberculosis, massive morbid obesity or severe psychiatric illness), 2) multiple gestation, 3) lethal fetal anomalies, and 4) low literacy. The exclusion criteria were set to limit the study participants as low-risk patients, which is consistent with both the GPNC model design and the scope of medical practice of nurse practitioners/nurse midwives who provide GPNC. Women who have participated in this study in a previous pregnancy will also be excluded, in order to maintain independence. Based on our preliminary data, application of these criteria will result in an estimated exclusion of 10% of women for late entry to care and 8% for pre-existing medical complications. The exclusion criteria will be applied to all women before randomization. We will track demographic characteristics and reasons for exclusion for women who are ineligible for the study as well as for those who are eligible but decline participation.

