### Analytic plan

Primary analyses for Aims 1, 2, and 3 will be conducted using an intent-to-treat approach. Study participants will be retained in their original assignment groups after the randomization in the analysis regardless of the number of missed visits, the use of additional services (e.g., progesterone), or loss to follow-up.
*Aim 1 analysis plan*: comparison of primary and secondary outcomes for GPNC vs. IPNC. To test the hypothesis for aim 1 that women who participated in GPNC will have a lower rate of PTB and other selected birth outcomes as compared to their counterparts in IPNC, multivariate regression models (logistic regression if the outcome is a binary variable and linear regression if the outcome is a continuous variable) will be employed with the intervention assignment as the primary independent variable. We will test the null hypothesis of coefficient of main exposure variable (GPNC vs. IPNC) equals zero. Stratified analyses will be conducted (e.g. race/ethnicity, previous history of PTB) to compare the primary and other outcomes within sub-groups.
*Aim 2 analysis plan*: comparison of racial disparities of primary and secondary outcomes for GPNC vs. IPNC. To test the hypothesis for Aim 2 that the Black-White differences in PTB and other selected birth outcomes is smaller in the GPNC as compared with that in IPNC, we will apply analyses similar to Aim 1 but adding an interaction term of prenatal care (GPNC vs. IPNC) with race (White vs. Black). We will test the null hypothesis of coefficient of interaction term equals zero. For aim 2, only women identified themselves as either Black or White will be included in the primary analysis. Then, we will conduct a sensitivity analysis to see whether including women who self-identified race as “Hispanic ethnicity”, “Mixed race” and “Other race” will influence the primary analysis results. Such sensitivity analysis will be guided by the results from the sub-groups analysis in Aim 1.

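### Aim 2 is sized by entering a Black-White risk difference as if it were an event rate; the claimed 90% power is really about 7-9%

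*Protocol article*

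**What the plan says.** Aim 2 asks whether the Black-White risk difference in PTB is smaller under group prenatal care (GPNC) than under individual care (IPNC).

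- **Sample size, Aim 2 input:** "For aim 2, assuming the proportion of PTB rate of 0.02, our study will need" 2,748 women (1,374 per group) to detect a 1.4-point reduction in the risk difference, at alpha 0.05 and 90% power.
- **Table 3 footnote:** P0 is "the RD of PTB in IPNC group". The text introducing the table likewise describes the Aim 2 P0 as a Black-White rate difference of 2% to 3%.
- **Sample size, conclusion:** "This sample size estimates that the proposed study will have 90% power to detect racial difference on PTB for Aim 2".
- **Analytic plan, Aim 2:** the test is a care-by-race interaction, and "For aim 2, only women identified themselves as either Black or White will be included in the primary analysis".
- **Patient population:** the expected mix is "45.8% non-Hispanic White, 25.5% non-Hispanic Black, 22.2% Hispanic and 6.5" per cent other.
- **Source of the 1.4 points:** Preliminary research says "the Black-White difference of PTB was 1.0% in the GPNC and 2.4% in the IPNC group". The Sample size section says "the risk difference of having PTB between Black women and White women was 1.0% in the IPNC and 2.4% in the GPNC".

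**The concern.** The section calls 0.02 a PTB rate, yet puts PTB in traditional care at 10-16% a few lines earlier. The table footnote shows what happened: a difference between two rates was put where a single rate belongs. A binomial variance at 2% is far smaller than one at 10-16%. A difference of differences also adds four variances, not two, and the smaller Black cells dominate the sum. The calculation further counts every enrolled woman, although the Aim 2 analysis excludes all who are not Black or White.

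Narrowing the disparity is a headline aim. The background and aims present the trial as having enough power to settle it, and Aim 2 supplies the larger of the two totals (2,748 against 2,712) from which the recruitment target is built. If power is far below 90%, a null Aim 2 result says almost nothing, but a reader who relies on the stated power could take it as evidence that group care does not narrow the gap. The section on interim analyses also proposes to monitor power for each hypothesis and perhaps stop collecting data once it is adequate, so a wrong power basis could affect conduct.

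**Working it through.** **1. Reproduce the printed figure.** The pooled two-proportion formula, two-sided alpha 0.05, 90% power, is

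n = [1.96·√(2p̄(1−p̄)) + 1.2816·√(p₀(1−p₀) + p₁(1−p₁))]² / (p₀−p₁)²

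With p₀ = 0.02, p₁ = 0.02 − 0.014 = 0.006 and p̄ = 0.013, n = 1,373.6, the printed 1,374. The formula also returns the other Aim 2 entries in Table 3 to within rounding. The one exception is P0 = 0.03, RD = 0.014 at 90% power, which computes to about 2,407 but is printed as 2,048. The risk differences were therefore entered as event proportions.

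**2. Set up the contrast Aim 2 states.** It is (Black − White in IPNC) − (Black − White in GPNC), with

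SE = √[Σ p(1−p)/n] over the four race-by-arm cells.

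Inputs from the protocol:
- 1,580 recruited per arm and 15% attrition: 1,580 × 0.85 = 1,343 evaluable per arm.
- White: 1,343 × 0.458 ≈ 615 per arm. Black: 1,343 × 0.255 ≈ 342 per arm.
- Both arms together: 3,160 × 0.713 × 0.85 ≈ 1,915 Black and White women.
- Risk differences of 2.4% (IPNC) and 1.0% (GPNC), hence 1.4 points.

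Assumption: the protocol gives no PTB rate by race and arm. The base case takes IPNC White 12.0% and Black 14.4%. GPNC White is 0.70 × 12.0% = 8.4%, using the Aim 1 relative risk, and GPNC Black is 9.4%.

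**3. Base case.**

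SE = √(0.12·0.88/615 + 0.144·0.856/342 + 0.084·0.916/615 + 0.094·0.906/342)
= √(0.000172 + 0.000360 + 0.000125 + 0.000249) = 0.0301

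- Standardised effect: 0.014/0.0301 = 0.465. Two-sided power: **7.5%**.
- Detectable with 90% power: (1.96 + 1.2816) × 0.0301 ≈ **9.8 points**.
- 95% confidence interval half-width: 1.96 × 0.0301 ≈ **5.9 points**.

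**4. Vary the assumptions.**

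| White IPNC rate (other inputs as above) | SE (points) | Power | Detectable at 90% power (points) | Black and White women per arm for 90% power |
|---|---|---|---|---|
| 8% | 2.6 | 8.5% | 8.3 | about 34,000 |
| 12% | 3.0 | 7.5% | 9.8 | about 46,500 |
| 15% | 3.3 | 7.1% | 10.6 | about 55,000 |

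- No overall GPNC effect (GPNC White rate equal to IPNC): about 6.8-8.0%.
- All 2,748 women Black or White, split 50:50: about 8-11%.
- Interaction on the logistic scale, the model the Analytic plan names for binary outcomes: about 6-8% with 1,343 evaluable per arm.

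**5. Check the planning inputs.** Preliminary research gives 2.4% in IPNC and 1.0% in GPNC; the Sample size section gives the reverse. As printed there, the preliminary data point against Hypothesis 2. Even the incorrect formula, given 0.024 versus 0.010, needs about 1,790 per group, more than the 1,580 to be recruited. At 1,374 per group it would give 81% power.

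**The case against.** Several points can fairly be made for the plan.

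- **The cell rates are assumed.** This is true, and it means the power cannot be given as one exact figure. The result is nevertheless stable: two-sided power stays between about 6% and 11% across the cases tried. Sidedness is not stated for Aim 2; a one-sided test would give about 11-17%, but only a two-sided test reproduces 1,374.
- **The risk-difference test above is not the planned model.** The Analytic plan tests a logistic interaction, which is a ratio of odds ratios, while Aim 2 is worded as risk differences. On the logistic scale power is no better.
- **The swapped 1.0% and 2.4% look like a slip in one sentence.** Preliminary research, Hypothesis 2 and the direction of the calculation agree with each other, and the swap changes neither the 1.4 points nor the 1,374. It needs correcting but is secondary.
- **P0 = 0.02 is a displayed choice.** Table 3 shows 0.02 and 0.03, which bracket the 0.024 from the preliminary data. The smaller value was the favourable one, but that matters little beside the wrong formula.
- **A journal article condenses.** Brevity can explain a missing derivation. It does not explain a printed number, table and power statement built on the wrong quantity.

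None of this restores the 90% claim.

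**Conclusion.** The concern holds. The 1,374 per group answers a different question: whether a 2.0% event rate differs from a 0.6% event rate. For the stated Aim 2 effect of 1.4 points, power is about 7-9% at the protocol's race mix and attrition, and at most about 11% two-sided in the most favourable case tried. The trial can detect with 90% power only a difference of differences of about 8-11 points, several times the IPNC disparity of 2.4 points it hopes to reduce. These figures rest on assumed race-specific PTB rates (White IPNC 8-15%), the 45.8%/25.5% mix and 15% loss. That the formula is wrong rests on no assumption, because the printed number reproduces exactly. This must be corrected.

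**What to change.** - Withdraw the 90% power statement for Aim 2 and the Aim 2 half of Table 3. Base the sample size on Aim 1 (2,712 women). After 15% loss, 3,160 recruited leaves 3,160 × 0.85 = 2,686, which is 26 short of that, so the Aim 1 inflation should be restated at the same time.
- State what Aim 2 can deliver: about 1,915 evaluable Black and White women, a 95% confidence interval half-width of about 6 points, and a detectable difference of differences of about 8-11 points, with the assumed cell rates shown. Presenting Aim 2 as an estimation aim is the simplest course. If the interaction test is kept, its low power should be stated beside it.
- Correct the Sample size section so that 2.4% belongs to IPNC and 1.0% to GPNC, as in Preliminary research.
- Remove the wording in Preliminary research and Specific aims that presents the trial as adequately powered or conclusive on race.

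The cost is wording in the protocol, and in the analysis plan if it repeats the claim. No further participants are needed. The stated prospects for Aim 2 become much less favourable.

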### Participant recruitment and screening

We propose to recruit and follow 3,160 (*N* = 1,580 in each group) pregnant women (see section for sample size calculations). Approximately 250 women begin prenatal care at the GHS OB Center each month, and 75% of them will be eligible for the proposed study (180 eligible women per month). The provider will screen all new patients presenting to the practice for prenatal care (at the first prenatal visit) for eligibility and to introduce the study to eligible women. Given our previous recruitment rate of 50%, we estimate that the targeted study sample size will be achieved in 3 years. At the time of the nurse education visit at the GHS OB Center, all patients will be screened for study eligibility based on review of medical records and a series of screening questions answered by the GHS intake nurses. The final eligibility screening will take place after the patient is scheduled with a healthcare provider. This may be the same day, or may be a separate day from the nurse education visit. Once the history and physical exam has been completed, the research nurses will approach eligible patients for study enrollment. Patients will be taken to a quiet space to have the study explained. The enrollment process involves a face-to-face interview with one of the study team for verification of study eligibility and counseling regarding study procedures, potential benefits and risks, prior to obtaining written consent. Recruitment began in July 2016 and will be monitored monthly. Figure 1 describes the flow of participants through the study recruitment and data collection.

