### Randomization and masking

#### Randomization

Women who are eligible for the study will be offered participation. Women who are interested in participation will have the opportunity to ask questions, confirm interest, provide consent, undergo group assignment, as well as complete the baseline data collection (Survey 1). Women who agree to participate will be randomized 1:1 to IPNC or GPNC based on computer-generated group assignment. These assignments will be stratified by race and ethnicity (Black, White, Hispanic, Mixed, and Other).

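### Minor: the target of 3,160 adds 15% to 2,748 instead of dividing by 0.85, so at 15% attrition it falls slightly short of both stated requirements

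*Protocol article*

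**What the plan says.** In the Sample size section, the Aim 1 statement begins "assuming the proportion of PTB rate of 13%, our study will need" and gives a total of "2,712 (1,356 in each group) to detect the relative risk of PTB in GPBC vs. IPNC of 0.70". The Aim 2 statement begins "For aim 2, assuming the proportion of PTB rate of 0.02, our study will need" and gives "2,748 (1,374 in each group) to detect reduction in risk difference of 1.4% between Black and White women". Both are set at a two-group alpha of 0.05 and 90% power.

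The next sentence sets the target: "With an estimated 15% attrition rate, we will target recruiting 3,160", split as 1,580 per group. The paragraph ends by claiming 90% power for Aim 2 at this sample size. The Participant recruitment and screening section repeats the target: "We propose to recruit and follow 3,160". The article does not say how the attrition allowance was applied.

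**The concern.** An attrition rate is the share of recruited women whose outcome is lost. To keep n evaluable women at a loss rate d, one recruits n/(1 − d). Multiplying by (1 + d) gives too few. If the target was obtained by multiplication, the recruitment number, the attrition rate, the evaluable numbers and the 90% power cannot all be true together, although they stand in adjoining sentences. Readers will use this paragraph to judge how informative a null result is, so its figures should agree.

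**Working it through.** **Inputs.** All are from the Sample size section except the allocation, which is from Randomization ("Women who agree to participate will be randomized 1:1 to IPNC or GPNC").
- Aim 1: control rate 0.13 and relative risk 0.70, so 0.13 × 0.70 = 0.091 in the group-care arm; 1,356 per group.
- Aim 2, as the plan sets it up: 0.020 versus 0.020 − 0.014 = 0.006; 1,374 per group.
- Alpha 0.05, power 90%, attrition 15%. Sidedness is not stated; two-sided reproduces the figures.

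**Step 1: reproduce the stated requirements.** Pooled-variance formula for two proportions, without continuity correction, where p̄ is the mean of p₁ and p₂:

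n per group = [1.960·√(2p̄(1−p̄)) + 1.2816·√(p₁(1−p₁) + p₂(1−p₂))]² / (p₁−p₂)²

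- Aim 1: p̄ = 0.1105; [1.960 × 0.4434 + 1.2816 × 0.4425]² / 0.039² = 1,356.
- Aim 2: p̄ = 0.013; [1.960 × 0.1602 + 1.2816 × 0.1599]² / 0.014² = 1,374.

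Both match the text and Table 3. A continuity-corrected version gives 1,407 and 1,514, which do not match.

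**Step 2: reproduce the target.**
- 2,748 × 1.15 = 3,160.2, and per group 1,374 × 1.15 = 1,580.1. These are the stated 3,160 and 1,580.
- Division instead gives 1,356/0.85 = 1,595.3, so 1,596 per group (3,192 in total) for Aim 1, and 1,374/0.85 = 1,616.5, so 1,617 per group (3,234 in total) for Aim 2. Neither total appears in the article.

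**Step 3: what 3,160 leaves at 15% attrition.**
- 3,160 × 0.85 = 2,686, or 1,343 per group.
- Aim 1: 2,712 − 2,686 = 26 short (13 per group).
- Aim 2: 2,748 − 2,686 = 62 short (31 per group).

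**Step 4: power at 1,343 per group.** Same formula, solved for power, with √1,343 = 36.647:
- Aim 1: (0.039 × 36.647 − 1.960 × 0.4434)/0.4425 = 1.266, so power is 89.7%.
- Aim 2: (0.014 × 36.647 − 1.960 × 0.1602)/0.1599 = 1.245, so power is 89.3%.

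**Step 5: attrition that 3,160 tolerates.**
- Aim 1: 1 − 2,712/3,160 = 0.1418, so at most 14.1%.
- Aim 2: 1 − 2,748/3,160 = 0.1304, so at most 13.0%.

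**Step 6: at the losses seen earlier.** The Retention plan reports 92% retention at delivery, and Preliminary research reports 89% through pregnancy.

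| Loss | Women remaining | Aim 1 power | Aim 2 power (plan's inputs) |
|---|---|---|---|
| 8% | 2,907 | 91.9% | 91.5% |
| 11% | 2,812 | 91.0% | 90.7% |
| 15% | 2,686 | 89.7% | 89.3% |

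**The case against.** **The effect is negligible against the planning uncertainty.** At relative risk 0.70 and 90% power, Table 3 runs from 1,814 per group (control rate 10%) to 1,070 (16%), a spread of 744. The Aim 1 shortfall is 13 per group. This stands, and it is why the point is minor.

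**Actual loss may be below 15%.** Preterm birth is known at delivery, and the earlier losses of 8% and 11% are both under 13.0%. The Compliance, cross-over, and follow-up section also plans to recover outcomes of women who deliver elsewhere, from medical records and state vital statistics. This lessens the concern but does not remove it. The same section counts miscarriage and delivery in another hospital system as loss to follow-up, earlier retention may not carry over, and 15% is the rate the plan chose.

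**The 15% could be meant as an add-on to the evaluable number.** That would make 3,160 consistent, but the loss it covers is then 0.15/1.15 = 13.0% of recruits. The article calls 15% the attrition rate.

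**Intent-to-treat analysis keeps every woman.** The Analytic plan keeps women in their assigned group despite loss to follow-up. That does not supply a missing outcome, and the plan itself inflates for attrition.

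**Stronger readings that do not follow.** A reader might infer that the trial will end up underpowered. The documents do not support this: the shortfall arises only at the full 15% and is under one percentage point of power. A reader might also infer that 74 more women (3,234 − 3,160) would secure Aim 2. That does not follow either. The 2,748 comes from treating Black–White risk differences as event proportions in whole arms, whereas the Aim 2 analysis tests an interaction among Black and White women only. Whether that calculation is valid is a separate question, and the attrition correction does not answer it.

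**Conclusion.** Wrong as written, and minor. The target reproduces as 2,748 × 1.15 in total and per group, and at the plan's own attrition rate it meets neither stated requirement. It is low by 32 recruits for Aim 1 (3,192 − 3,160, about 1.0%) and by 74 for the plan's Aim 2 figure (3,234 − 3,160, about 2.3%). Power falls by 0.3 points for Aim 1 and 0.7 points for Aim 2.

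This rests on three assumptions: a two-sided test by the formula that reproduces Table 3, attrition meaning the share of recruited women without an outcome and equal in both arms, and the Aim 2 inputs taken at face value. It does not threaten the Aim 1 comparison and gives no reason to change recruitment.

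**What to change.** Keep 3,160 and make the paragraph consistent in one of two ways.

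1. State that 15% attrition leaves 2,686 evaluable women (1,343 per group), with power of 89.7% for Aim 1 (13% versus 9.1%) and 89.3% for Aim 2 on the plan's inputs. Amend the closing sentence that claims 90% power for Aim 2 to match.
2. Replace the 15% by the rate that the target supports: 3,160 meets both stated requirements with at most 13.0% attrition (14.1% for Aim 1 alone). Cite the earlier losses of 8% at delivery and 11% through pregnancy as support for the lower rate.

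A restatement for Aim 1 only would not be enough, because 3,160 was derived from the Aim 2 figure. The cost is a sentence or two in the Sample size section. The target in Participant recruitment and screening, the design and the analysis stay as they are. Under the first option the stated power becomes marginally less favourable.
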